### Sample size

Sample size estimation for this study was informed by a recent benchmarking study (unpublished at the time of ethics submission) which assessed multiple LLMs on their ability to answer medical questions posed by CHWs. The primary performance metric used in the benchmarking exercise—alignment with expert medical consensus—closely approximates this study’s primary outcome: the appropriateness of referral decisions made by CHWs and the LLM compared with a clinical reference standard.

In the benchmarking dataset, GPs were estimated to make correct referral decisions in 73.3% of cases.^10^ This figure was, therefore, used as a conservative estimate of the referral decision accuracy for CHWs operating without LLM support in our study. In real-world practice, CHW accuracy may be lower than this benchmark, and thus this assumption yields a conservative estimate for sample size requirements by potentially underestimating the true effect size.

The same benchmarking study generated accuracy estimates for five leading LLMs (n=400 cases per model). Accuracy varied across models, with performance reported as follows: Gemini-2 (92.0%), GPT-4o (91.2%), o3 mini (91.0%), Deepseek R1 (83.8%) and Meditron-70B (79.7%). These results suggest that even under conservative assumptions, a performance difference of 15–20 percentage points between CHWs and high-performing LLMs is both plausible and likely detectable.

To estimate the number of interactions required to detect a given improvement in referral decision accuracy, sample size curves were generated for different effect sizes, assuming varying numbers of interactions per CHW per week (based on expected consultation volumes of 7–15 per week). These calculations suggested that, to detect a 15 percentage point increase in referral accuracy over the baseline of 73.3%, between 147 and 1064 total interactions would be required, depending on CHW workload and clustering. To detect a 20 percentage point improvement, between 49 and 392 consultations would be needed. These ranges assumed minimum cluster sizes of 7 interactions per CHW and accounted for clustering in the analysis.

Based on these projections, we plan to collect a total of 800 consultation transcripts, split evenly between two CHW cohorts: 400 recordings from CHWs using paper-based guidelines and 400 from CHWs using the CHWApp digital decision-support tool. To achieve this, we will recruit 50 CHWs per arm, each expected to contribute approximately 10 consultations. This recruitment target allows for a 20% attrition rate, due to technical failure, low recording quality or CHWs submitting fewer than seven recordings (the minimum cluster size for inclusion in analysis). We, therefore, anticipate that 40 CHWs per group will contribute usable data, with an average of 10 transcripts each, yielding the required 400 consultations per arm.

This sample size also allows for robust subgroup analyses and maintains adequate power to detect an absolute difference in referral accuracy as small as 11.8 percentage points—a conservative estimate given the larger effect sizes observed in benchmarking data.

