**Methods and analysis:**

This is a prospective, observational study conducted in Nyabihu and Musanze districts, Rwanda. Audio recordings of CHW-patient consultations will be transcribed and analysed by an LLM to generate referral decisions, differential diagnoses and management plans. These outputs, alongside CHW decisions, will be evaluated against a clinical expert panel’s consensus. The primary outcome is the appropriateness of referral decisions. Secondary outcomes include diagnostic accuracy, management plan quality, and patient and user perceptions to ambient recording of consultations. Sample size is set at 800 consultations (400 per district), powered to detect a 15–20 percentage point improvement in referral appropriateness.

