### LLM output generation

The recording and transcript will be automatically uploaded and accessed on a secure data warehouse. The first 10–20 transcript samples will be considered a pilot and excluded from the primary analysis. Instead, they will be used to assess recording quality and transcription accuracy, perform exploratory analysis and prompt engineering of the LLM (GPT-4). This process will involve examining the initial transcripts to optimise the LLM’s performance in generating useful outputs and refining how the prompts are structured to elicit the most accurate and relevant responses. By testing and adjusting the prompt structures based on these transcripts, we will effectively ‘tune’ the LLM to improve its clinical decision-making capabilities.

Following this, the research team will omit the interaction’s outcomes (ie, the CHW’s management and referral decision) and feed the transcript and prompts to the LLM to: (1) produce a referral decision, (2) suggest five differential diagnoses in order of likelihood and (3) propose a management plan

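### The power statements for 11.8 and 15 percentage points are unqualified, although by the plan's own range 800 consultations secure them only under part of the clustering and workload assumptions

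*Protocol article*

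**What the plan says.** The Sample size section takes 73.3% as baseline accuracy for community health workers (CHWs). It borrows this from a benchmarking study in which "GPs were estimated to make correct referral decisions in 73.3% of cases".

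For a 15-point gain over that baseline, it says "between 147 and 1064 total interactions would be required, depending on CHW workload and clustering". For the larger effect, it says "To detect a 20 percentage point improvement, between 49 and 392 consultations would be needed". Both ranges are described as allowing for clustering, with at least 7 interactions per CHW.

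On the strength of these projections, "we plan to collect a total of 800 consultation transcripts, split evenly between two CHW cohorts". This is built up as 40 usable CHWs per cohort with about 10 transcripts each. The section adds that this number allows robust subgroup analyses and "maintains adequate power to detect an absolute difference in referral accuracy as small as 11.8 percentage points".

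The abstract describes the study as "powered to detect a 15–20 percentage point improvement in referral appropriateness". Neither power statement names the workload or clustering assumption under which it holds.

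**The concern.** A smaller difference needs more consultations than a larger one. If 15 points can need as many as 1064, then 800 cannot secure 15 points under every assumption the plan considered, and it is further from securing 11.8. Yet both are stated as plain properties of the design.

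What is at stake is how a modest or null difference between the large language model (LLM) and the CHWs will be read. A reader told that the study could detect 11.8 points would take a non-significant result as evidence against a gap of that size. At the upper end of the plan's clustering range the study would not support that reading. The same applies, more strongly, to comparisons within one cohort of 400.

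**Working it through.** **Inputs from the Sample size section.** Baseline 73.3%; 147–1064 consultations for 15 points; 49–392 for 20 points; 800 planned, 400 per cohort; 10 transcripts per CHW. The article does not give alpha, sidedness, power or intracluster correlation (ICC). I assume alpha 5% and show both 80% and 90% power.

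**Can the plan's figures be reproduced?** Not uniquely.
- The pooled two-proportion formula (two-sided 5%, 80% power) needs 185 per group for 11.8 points, 108 for 15 and 54 for 20, before clustering. The plan's lower limit of 49 for 20 points is already below 54.
- One-sided, the formula needs 85 per group for 15 points and 42 for 20. The lower limits then imply design effects of 147/85 = 1.73 and 49/42 = 1.17, which do not match.
- The plan's ratios of 15-point to 20-point requirements are 147/49 = 3.0 and 1064/392 = 2.7. The formula gives 108/54 = 2.0.

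**Coverage read directly from the stated ranges (no formula needed).**

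| Effect | Stated requirement | 800 overall | 400 per cohort |
|---|---|---|---|
| 20 points | 49–392 | covered throughout | covered throughout |
| 15 points | 147–1064 | not in scenarios needing 801–1064 | not in scenarios needing 401–1064 |

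**Power for 15 points at the upper limit.** With the effect and clustering fixed, precision scales with the number of consultations. Power at 800 is therefore Φ((z_α + z_β)·√(800/1064) − z_α), where √(800/1064) = 0.867.
- Curves at 80%, two-sided: Φ(2.802 × 0.867 − 1.960) = Φ(0.47) = 68%. One-sided: about 70%.
- Curves at 90%, two-sided: Φ(3.242 × 0.867 − 1.960) = Φ(0.85) = 80%. One-sided: about 81–82%.

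This step does not depend on which two-proportion formula the plan used.

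**Where 11.8 points sits in the range.** Moving from 15 to 11.8 points does need a variance formula. I use n ∝ (p₁q₁ + p₂q₂)/d².
- 15 points: (0.1957 + 0.1033)/0.0225 = 13.29.
- 11.8 points: (0.1957 + 0.1268)/0.01392 = 23.16.
- Ratio: 23.16/13.29 = 1.743.

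If 800 just detects 11.8 points, 15 points needs 800/1.743 = 459 (463–467 with the pooled formula). That is inside 147–1064 and well below the top. At the upper limit, 11.8 points would need about 1064 × 1.743 = 1854 (about 1820–1840 with the pooled formula). These values are approximate, because the formula does not reproduce the plan's limits.

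**Clustering under which 11.8 points is attainable.** With 10 per CHW the design effect is 1 + 9·ICC.
- 400 against 400, 80% power: 400/185 = 2.16, so ICC = 1.16/9 = 0.13. At 90% power: 400/247 = 1.62, so ICC = 0.07.
- 800 decisions of each type, 80% power, ignoring any gain from pairing: 800/185 = 4.32, so ICC = 3.32/9 = 0.37.

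**Does workload explain the upper limit?** The plan considers 7–15 consultations per CHW per week and expects about 10 per CHW in total. Suppose 1064 belongs to clusters of 15. Going to 10 can shrink 1 + (m − 1)·ICC by at most a factor of 10/15, so 15 points would need at least 1064 × 10/15 = 709, which 800 could cover. For 11.8 points the requirement would still be at least 709 × 1.743 = 1236. If instead 1064 belongs to clusters of 7, going to 10 raises the requirement at any positive ICC. The article does not say which applies.

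**The case against.** The strongest defence is that 147–1064 is a range over assumptions, and 800 lies inside it at 75% of the upper limit. The 11.8 figure is one point within those assumptions and is attainable at ICCs that are not extreme. That stands. A reader might infer that the plan contradicts itself, or that 800 detects roughly 15–17 points rather than 11.8. The document does not support either: that reading treats the single worst scenario as the design.

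It is also fair that the scaled figures rest on an unpaired formula that does not reproduce the plan's limits, while the LLM and CHW decisions are made on the same consultations. For this reason the 11.8-point extrapolations are indications only and should not become replacement values. The direct comparison of 800 with 1064, and the power for 15 points, do not depend on that formula. If the curves used 90% power, about 80–82% for 15 points at the upper limit would ordinarily be acceptable. The shortfall there would be modest.

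Three further inferences are tempting but do not hold.
- Calling 11.8 points conservative is not a claim about clustering. The text compares it with the benchmark effect sizes, and the three best models do show larger gaps (17.7 to 18.7 points).
- The benchmark does not cap the plausible effect at 18.7 points. The 73.3% is an accuracy for general practitioners, and the article says CHW accuracy may be lower.
- Naming GPT-4 as the study model while the benchmark lists GPT-4o does not affect this arithmetic.

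Finally, an article may leave the ICC, alpha and power to the full protocol. Their absence is not the point. The point is that two published power statements are broader than the published range allows.

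**Conclusion.** The point holds as one of qualification, not of contradiction. By the plan's own range, 800 consultations cover 20 points throughout. They cover 15 points except in scenarios needing 801–1064, and 11.8 points only under moderate clustering, where 15 points would need about 460. At the upper limit, power for 15 points is about 68–70% (80% curves) or 80–82% (90% curves). Within one cohort of 400, 20 points is covered throughout and 15 points is not at the upper end, so the subgroup claim is also unqualified.

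The coverage statements rest only on the article's figures. The power values assume alpha 5% and a normal approximation. The 460 figure and the ICC thresholds also assume an unpaired comparison from 73.3%. Pairing would change the absolute numbers, but not the fact that 800 is below 1064. This warrants a correction of the text; it does not threaten the design.

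**What to change.** Keep 800 consultations.

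1. Recompute the detectable difference for the design as it will be run: both decisions on the same consultations, about 80 CHWs with about 10 each, under one stated clustering assumption consistent with the Sample size range.
2. Restate the 11.8-point figure and the abstract's 15-point claim as holding under that assumption.
3. Give alongside them the detectable difference at the upper end of the clustering range, for 800 overall and for 400 per cohort.
4. Qualify the description of the subgroup analyses as robust to match: 20 points per cohort is covered across the stated range, 15 points is not.

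The approximate values in the check above should not be copied in as the new figures.

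The cost is one recalculation, a few sentences of text, and a detectable difference that reads less favourably or carries a condition. No consultations, CHWs or analyses are added.

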### Statistical analysis plan

Descriptive statistics will be used to summarise the demographic characteristics of participants and key measures.

#### Primary outcome analysis

The primary analysis will involve (1) assessing the LLM’s performance (accuracy) in relation to the ground truth and (2) assessing the LLM’s accuracy compared with the CHW’s performance alone.

All model performance metrics, including accuracy, sensitivity, specificity, positive predictive value and negative predictive value (NPV) and their corresponding confidence intervals will be calculated from information on numbers of true positive, false negative, false positive and true negative model allocations included in the standard 2×2 (confusion) matrix, as shown in figure 2. Note here that the term ‘positive’ indicates a decision to refer the patient, and the term ‘true’ indicates that this decision was appropriate. See online supplemental material for further details on performance metrics.

**Figure 2 F2:**
[figure not shown]
Confusion matrix used in statistical analysis. CHWApp, Community Health Worker Application; LLM, large language model.

The performance of the LLM will first be assessed in comparison to the current CHW-only referral approach across the full evaluation data, with no accounting for clustering by geographic location. However, to examine heterogeneity, model performance will also be summarised across natural clusters (defined by CHW as a proxy for geographic location) using a one-stage multivariate meta-analysis approach. Separate one-stage bivariate random-effects logit-normal models will be fitted, with the first jointly synthesising recall and specificity and the second incorporating both precision and NPV.^11 12^ These bivariate meta-analysis models will be extended to incorporate a test-type indicator (LLM vs CHW only) as a meta-regression component to inform the assessment of the difference in referral accuracy between the two referral decision types.^12^ Additional meta-regression components will also be included to adjust the analysis for other important consultation factors, such as whether the consultation involved a paper or app-based decision tree.

A secondary analysis will also be conducted using an extended trivariate model (jointly synthesising recall, specificity and prevalence), with transformations to the predicted probabilities (precision, NPV) following pooling using Bayes Theorem.^12 13^ Values of each of the above performance statistics will be calculated for the LLM and the CHW referral decisions and will be presented with 95% CIs and indications of heterogeneity across CHWs (τ^2^, 95% prediction intervals).

### Secondary outcome analysis

Referral decision appropriateness will be reassessed following integration of day 5 and day 14 follow-up outcome data. The expert panel’s revised appropriateness assessment incorporating these outcomes will serve as an updated reference standard. Diagnostic accuracy metrics and paired comparisons will be repeated against this outcome-informed standard.

For cases with a definitive diagnosis established through expert panel consensus or counter-referral documentation, the proportion of correct diagnoses appearing as the LLM’s top-1 and within its top-5 differential diagnosis list will be reported, with 95% CIs.

Outcomes of interest (appropriateness of differential diagnosis and appropriateness of management plan) will each be measured on a 5-point Likert scale. Distributions of these Likert scale responses will be displayed using frequency tables, numerically summarised across interactions using the median, along with upper and lower quartile values, and visualised using histograms, demonstrating the proportion of interactions rated to be at each level of the scale. For each secondary outcome separately, a multilevel ordinal regression model will be fit, adjusting for important consultation features, with a random effect on the intercept term to account for the natural clustering of the data, as discussed above. Secondary outcome involving measuring the top-1 and top-5 diagnostic accuracy for a subset of participants where a definitive diagnosis was made. The mean (median) rank of the ground truth diagnosis in the differential list will also be summarised.

The patient and CHW user experience questions will be analysed with descriptive analysis to assess the acceptability and impact of recordings. Qualitative responses from CHWs will be thematically analysed to generate themes.

### Data monitoring

All recorded consultations will be automatically uploaded to a secure, password-protected data server hosted by the Centre for the Fourth Industrial Revolution (C4IR) in Kigali. Audio files will be transcribed and translated from Kinyarwanda to English using a purpose-built AI-based translation system developed by a local technology partner.

The LLM’s outputs will be securely stored and linked to the corresponding anonymised consultation record for later comparative analysis.

### Data quality assurance

The quality and completeness of all collected data will be routinely monitored by the study management team. Daily data quality checks will be conducted to verify data upload eligibility, completeness and audibility. Cases with missing history and/or referral outcome in the recording will be automatically discarded. Any missing demographic data will be addressed with the respective CHWs via phone call to fill in retrospectively. Only cases that fulfil the above criteria will be forwarded for transcription, translation and LLM prompting. Follow-up adherence will be assessed weekly. Cases that have no follow-up data will not proceed for evaluation. Instead, CHWs will be prompted to conduct the missing follow-up.

A random sample of 20% of audio recordings will be reviewed by independent Kinyarwanda-speaking researchers to cross-validate machine-generated transcripts, with an acceptable error threshold set at <15%. Any breach of this threshold will trigger a data quality review by the study steering committee to determine whether data collection should continue or changes are required.

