### Follow-up and related events

As part of standard CHW practice, patients will be followed up on day 5 to assess symptom progression and treatment outcomes. In addition, the study protocol includes a day 14 follow-up for research purposes. CHWs will complete a structured follow-up form (see online supplemental material 1) on the StudyApp, capturing information on symptom resolution (resolved, unchanged, worsened, deceased), any further health service use and counter-referral details for referred patients.

Patients reporting full symptom resolution at the day 5 follow-up will not undergo the day 14 follow-up. CHWs will also photograph and upload any counter-referral forms (providing feedback to the CHW for continued care in the community) received from health centres for referred patients (see online supplemental material 1).

After the data collection period, RAs will conduct short user experience surveys and four focus group discussions of 8–12 CHWs to get insight into their experience of being recorded and any challenges faced (see online supplemental material 1).

Patient participant flow is summarised in figure 1.

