### Expert evaluation of CHW outputs and LLM outputs

12 independent GPs, each with a minimum of 2 years of clinical experience in Rwanda and valid Rwanda Medical and Dental Council licences, will be recruited for this study. They will be organised into four panels of three to evaluate each patient–CHW consultation transcript using a study-specific evaluation rubric (see online supplemental material 1). This evaluation will provide a ground truth against which the LLM and CHW outputs will be measured. Evaluators will receive training to standardise the evaluation approach. This training will include an overview of the study protocol and detailed instructions on using the evaluation rubric. During the training, 10 simulated cases will be reviewed to establish a common frame of reference across the panel and to familiarise evaluators with the rubric.

Everyone in the triplet group of evaluators will independently review the case transcript, make a diagnosis and develop a management plan. The evaluator’s tasks for each objective are as follows:

Based only on the day 0 consultation transcript, a reference standard should be determined to decide on the appropriateness of the CHW and LLM referral decisions.Review the day 0 consultation transcript and the 5-day or 14-day follow-up information to establish a reference standard for evaluating the correctness of the CHW and LLM referral decisions.Assess the diagnostic accuracy of the LLM through:

 Establishing one ‘most likely’ diagnosis based on all the information provided. Independently scoring the appropriateness of the differential diagnosis list according to a prespecified rubric. Assessing whether the diagnosis provided in the counter-referral (or, if unavailable, the panel’s ‘most likely’ diagnosis) is the top-ranked or is included within the top five differential diagnoses suggested by the LLM.

4. Assess the appropriateness of the LLM-generated management plan according to the evaluation rubric.

After the initial assessments, the average response for the Likert scale question will be calculated. The panel will also review and discuss the open-ended responses, such as the ‘most likely’ diagnosis, and collaboratively reach a consensus on the diagnosis.

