### Primary outcome

The primary outcome of this study is the appropriateness of referral decisions made by CHWs and by the LLM, measured against the consensus decision of an independent expert clinical panel, according to the day 0 consultation transcript only.

For each patient consultation, both the CHW’s actual referral decision on whether to refer the patient to a health facility or manage them in the community and the LLM-generated referral decision will be compared with the reference standard established by a blinded evaluation panel of GPs, based solely on the information available in the day 0 consultation transcript.

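### Cases whose follow-up stays missing drop out of the primary LLM–CHW comparison, although that comparison uses only day 0 data

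*Protocol article*

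**What the plan says.** The Primary outcome section compares the CHW's decision and the LLM's decision with a panel standard "based solely on the information available in the day 0 consultation transcript". The first evaluator task, under Expert evaluation of CHW outputs and LLM outputs, agrees: "Based only on the day 0 consultation transcript, a reference standard should be determined". Follow-up enters at the second task, which serves the outcome-informed secondary comparison: "Review the day 0 consultation transcript and the 5-day or 14-day follow-up information".

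The Data quality assurance section then sets the data flow: "Cases that have no follow-up data will not proceed for evaluation". The next sentence adds a recovery step: "Instead, CHWs will be prompted to conduct the missing follow-up". No rule covers follow-up that is still missing after the prompt.

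Under Follow-up and related events, CHWs complete the follow-up form. Day 5 is standard practice; for day 14 the section says "In addition, the study protocol includes a day 14 follow-up for research purposes". That second contact is not always due: "Patients reporting full symptom resolution at the day 5 follow-up will not undergo the day 14 follow-up".

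The Sample size section plans 800 transcripts, 400 per cohort, after a 20% attrition allowance. It attributes that allowance to technical failure, poor recordings and CHWs with fewer than seven recordings.

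**The concern.** The primary comparison needs three things: the CHW's decision, the LLM's decision and the panel's day 0 judgement. All three can be had without follow-up. The data-flow rule nevertheless makes follow-up a condition of panel evaluation in general, so the primary sample is selected on something that happens after the decisions being judged.

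The selection may not be neutral. The CHW whose referral decision is assessed is also responsible for the follow-up record. If CHWs who follow up less completely also refer better or worse than others, or if their cases differ in difficulty, the retained consultations do not represent those recorded. The estimate at stake is the main LLM–CHW difference. A lesser matter is that usable consultations are lost for a reason the sample-size section did not allow for.

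**Working it through.** **1. The rule against the outcome.** The primary outcome and the first evaluator task use the day 0 transcript only. The second evaluator task uses day 0 plus follow-up. The data-flow rule applies to evaluation without distinguishing the two tasks. Read literally, it bars a case from the first task for want of data that only other tasks use.

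**2. The plan's own yield.** Inputs from the Sample size section: 50 CHWs per arm, 20% attrition, about 10 consultations each.

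- 50 × (1 − 0.20) × 10 = 400 per arm; 400 × 2 = 800.

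The stated figure reproduces exactly, and the 20% is fully used by the causes the plan lists. Missing follow-up is not among them.

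**3. Consultations left after the rule.** The documents give no rate of unrecovered follow-up, so the loss L is an assumption. Remaining = 800 × (1 − L). The last column assumes that the minimum of seven per CHW is applied after this rule, with 10 recordings per CHW and independent losses (binomial).

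| L | Remaining | Remaining if the seven-case minimum follows |
|---|---|---|
| 5% | 760 | about 760 |
| 10% | 720 | about 714 |
| 20% | 640 | about 585 |
| 30% | 560 | about 409 |

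**4. Precision.** The section gives no alpha, power or intracluster correlation (ICC), so the stated 11.8-point detectable difference cannot be checked exactly. An unpaired two-proportion yardstick was used: 73.3% baseline, two-sided 5%, 400 per group, design effect 1 + (10 − 1) × ICC. On that basis 11.8 points corresponds to an ICC of about 0.13 at 80% power or 0.07 at 90%. It is attainable and is not disputed.

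With ICC 0.10 and 80% power (both assumed), and with cluster size shrinking to 10 × (1 − L), the detectable difference is:

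- L = 0: 11.1 points
- L = 10%: 11.4 points
- L = 20%: 11.7 points
- L = 30%: 12.1 points

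These do not apply the seven-case minimum. All are below the 15 points targeted.

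**5. Selection.** Let D be the LLM–CHW accuracy difference in all recorded consultations and D_lost the difference in the lost ones.

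- Retained difference = (D − L × D_lost) / (1 − L)
- Shift = [L / (1 − L)] × (D − D_lost)

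Take CHW accuracy of 73.3% (the plan's assumption) and D = 15 points (the lower end of the plan's range). If CHW accuracy in lost cases is 10 points lower and LLM accuracy is unchanged, D_lost = 25:

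- L = 10%: (0.10 / 0.90) × (15 − 25) = −1.1 points
- L = 20%: (0.20 / 0.80) × (15 − 25) = −2.5 points

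A 20-point gap gives −2.2 and −5.0. If CHW accuracy in lost cases is higher instead, the same sizes apply with the opposite sign. If both decision-makers are worse by the same amount in lost cases, D_lost = D and the shift is zero.

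**The case against.** The strongest reply is that the rule is hold-and-chase, not exclusion. Follow-up adherence is checked weekly, CHWs are prompted, and recovered cases can proceed. Residual loss is also limited elsewhere. The eligibility criteria exclude patients who cannot or will not be contacted, or who would not attend a health centre if referred. Day 5 contact is routine, a day 5 record alone may satisfy the rule, and death is a recordable status. All of this stands. A reader might infer that every case without follow-up at first check is lost for good; the text does not support that. What remains is the case still missing after the prompt, which the rule leaves unevaluated.

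A second reply is that bias is not shown, and that is also right. A reader might infer that the rule flatters CHW accuracy because less diligent CHWs' cases drop out. No section says that missing follow-up marks worse referral decisions. If lost cases had 85% CHW accuracy, measured accuracy would fall: (0.733 − 0.10 × 0.85) / 0.90 = 72.0%, and (0.733 − 0.20 × 0.85) / 0.80 = 70.4%. Each lost case also removes both paired decisions, so a movement in CHW accuracy alone is not a movement in the difference.

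A reader might extend the criticism to the neighbouring rule, "Cases with missing history and/or referral outcome in the recording will be automatically discarded", and propose taking the decision from CHWApp or paper records. The article does not show that the study collects or links those day 0 records, so this could mean new data collection. Discarding incomplete recordings is a defensible completeness check. The point does not extend to it.

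**Conclusion.** The point holds in limited form. The data-flow rule is wider than the primary outcome requires, and as written it makes the primary sample conditional on a later event recorded by the CHW under assessment. It should be fixed, but it does not by itself undermine the study.

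The size and direction of any bias cannot be determined from the documents. The illustrative shifts of about 1.1 and 2.5 points rest on three assumptions: unrecovered loss of 10% or 20%, a 10-point gap in CHW accuracy between lost cases and the overall 73.3%, and no gap for the LLM. The 73.3% is itself a benchmark figure for GPs that the plan uses in place of a CHW figure. The fall from 800 to 720 or 640 rests on the same assumed losses, and its cost in precision is modest. The case for change is avoidable selection in the primary sample more than lost power.

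**What to change.** Amend the data-flow rule in Data quality assurance so that every consultation passing the day 0 quality checks goes to the panel for the day 0 referral judgement. Require follow-up only for the outcome-informed secondary evaluation, keep the prompt to CHWs, and report how many consultations lack follow-up there.

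The cost is about one sentence and a few more panel reviews within the planned 800. No new data are collected, because the recordings already exist. The small downside is that some cases will have a day 0 evaluation without the follow-up-based tasks, so the primary and secondary comparisons will rest on slightly different sets of consultations.
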